## Abstract

Background

Self-medication (SM), a common practice globally, possesses a dual challenge of being a self-care strategy and a potential source of harm observed across all age groups. The study is being conducted to gauge the prevalence of SM of prescription drugs with their over-the-counter access, thus addressing the delicate balance between self-care and self-harm related to SM.

Material and methods

This ongoing convergent parallel mixed method study with quantitative and qualitative components will be conducted on a sample size of 180 subjects aged more than 18 years from an urban community. For the quantitative component, a semi-structured questionnaire will assess the prevalence of SM, types of medications used, reasons for self-medicating, and socio-demographic factors influencing these practices. Concurrently, qualitative interviews delve deeper into the beliefs shaping SM practices. Sampling will be purposive to capture diverse perspectives, with data analyzed using statistical tools.

Results

This study protocol will offer a comprehensive understanding of the prevalence and determinants of SM practices. The quantitative data provide numerical insights into SM trends, while the qualitative findings elucidate the nuanced factors driving individuals' SM choices.

Conclusions

A multifaceted view of SM practices will be provided, aiding in developing interventions to promote safe and effective self-care while mitigating the risks of self-harm through SM. Anticipated findings can include a widespread prevalence of SM amongst the general urban populace. Significant associations can also be expected to be found with various independent variables. The results will be instrumental in informing public health policies and healthcare practices toward enhancing patient safety and well-being.

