
## Materials and methods

Study design, participant, and setting

A convergent parallel mixed method study design with a quantitative component as a cross-sectional study and a qualitative component as an in-depth interview will be used for data collection for a period of 24 months from urban communities and pharmacies of Wardha. Before data collection, informed consent from study participants will be obtained, clearly outlining the purpose of the study, benefits and potential risks, voluntary participation, and the right to withdraw at any time. Ensuring participant confidentiality and privacy while collecting data is essential, and any ethical considerations or limitations in data collection will be carefully addressed to uphold research ethics standards. The study sought approval on 01.03.2024 from the Institutional Ethics Committee of Datta Meghe Institute of Higher Education and Research with reference number DMIHER(DU)/IEC/2024/126 to ensure the research adheres to the ethical guidelines, respects participant rights, and meets established ethical standards and has been registered for the Clinical Trials Registry - India with the registration number CTRI/2024/07/069886.

Inclusion and exclusion criteria

Subjects over 18 years and above who reside in Wardha and visited the pharmacy outlets to purchase medicine(s) during the study will be included in the study. Individuals participating willingly, voluntarily, and providing informed consent, who have a history of SM or are currently engaging in SM practices, and who have the cognitive ability to understand and respond to questions and participate in qualitative interviews. Doctors and healthcare workers who have knowledge of medications, individuals with cognitive impairments, and pregnant or breastfeeding women will be excluded from the study.

Sample size

The sample was calculated based on,

n = [Z2 P (1-P)]/d2

Z is the statistic corresponding to the level of confidence,

P is the expected prevalence,

d is precision (corresponding to effect size).

Sample size calculation

Assumptions:

Precision = 5.0% (0.05)

Prevalence = 11.9% (0.10) [16]

Z = 1.96

N = 1.96*1.96*0.119 (0.881)/0.0025

The final sample size based on the prevalence of 11.9% was 161. Assuming 10.0%-12.0% dropouts, the estimated sample taken was 180.

Data collection tools and methods

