## Discussion

Many factors can lead people to take their own medication, including the need for self-care, empathy for sick family members, a lack of health services, poverty, misinformation, misbelief, and the accessibility of medications in places other than pharmacies. Research conducted in two phases in India has indicated the prevalence of SM among students to be 74.6% and 69.4% [17]. Similar studies suggest that literacy level, history of SM, profession, unavailability of medical insurance, lack of priority in consulting medical professionals, low economic status, the female sex, and staying in an urban setting were among the factors associated with SM practices [17]. Given the growing public health concerns around SM with prescription drugs and OTC access, this study focuses on risk practice prevalence, its use, its safety, and reasons for using it. On one side, the availability of medicines on an OTC basis improves access to healthcare for people living in settings lacking in resources or in places in need of adequate healthcare infrastructure. On the other, it increases the probability of severely harming one's health by the misuse of medications [7]. The dichotomy needs thorough investigation, allowing us to balance accessibility and responsible drug consumption. It is essential for individuals using medications to have appropriate medical comprehension regarding dosage, timing of administration, and potential ramifications of overuse, as inadequate information could lead to major repercussions, including antibiotic resistance, skin issues, hypersensitivity, allergies, and dependency. As it stands, regulations around the OTC availability of certain prescription drugs vary globally across jurisdictions. There is an urgent need to enhance awareness and enact regulations aimed at promoting prudent and safe practices regarding SM. There is a potential to encourage its rational use and mitigate the emergence of microbial resistance by fostering and improving its knowledge. Despite existing research on this subject, SM has slipped under the radar regarding receiving the attention it warrants as a research area. Moreover, most studies on this topic have been conducted in countries with vastly different healthcare systems and cultural contexts from that of India, rendering their findings potentially non-transferable. It is imperative to gather data on the prevalence of SM in India as well as explore their related factors to facilitate the enhancement of SM practices within the country.

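### A survey confined to people buying medicine at pharmacies cannot give a community prevalence of self-medication, and its ±5-point precision loses its meaning if the stated purposive sampling governs the survey

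*Protocol article*

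**What the plan says.** **Aim and population.** For the quantitative part, the Abstract says that "a semi-structured questionnaire will assess the prevalence of SM". It describes "a sample size of 180 subjects aged more than 18 years from an urban community", and its conclusions add: "Anticipated findings can include a widespread prevalence of SM amongst the general urban populace". The end of the Introduction also gives prevalence estimation as the aim.

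**Who can enter.** Under Inclusion and exclusion criteria in Materials and methods, subjects who "reside in Wardha and visited the pharmacy outlets to purchase medicine(s) during the study will be included in the study". The next sentence lists willing, consenting individuals "who have a history of SM or are currently engaging in SM practices".

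**How they are chosen.** The Abstract states: "Sampling will be purposive to capture diverse perspectives, with data analyzed using statistical tools". Materials and methods gives no other method for the 180.

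**How many.** The Sample size section uses n = Z²P(1−P)/d² with Z = 1.96, P = 11.9% and d = 0.05. It arrives at 161, raised to 180 for 10% to 12% dropout.

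**What is conceded.** The Limitations paragraph says that sampling bias may limit the findings if the sample turns out not to represent the wider adult population of Wardha.

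**The concern.** The population in the aim and the population that can be enrolled differ. Buying medicine at a pharmacy is a condition of entry, and it is plainly related to the behaviour being measured. The Discussion itself names, among the drivers of SM, "the accessibility of medications in places other than pharmacies", and the Introduction makes the same point. People supplied only by that route are outside the frame, as are people who buy nothing.

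The precision formula is a second, separate matter. A half-width of ±5 points comes from independent, equal-probability sampling of the population to which the estimate refers. A purposive sample has no known inclusion probabilities, so an interval computed from it has no design-based coverage.

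Prevalence is the headline result and is meant to inform policy. A figure with a ±5-point interval, reported as the prevalence in the urban population, would be given a meaning that the design cannot support.

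**Working it through.** **1. The plan's own figure.** n = 1.96² × 0.119 × 0.881 / 0.05² = 161.1, which reproduces 161. Dropout: 161/0.90 = 179, 161/0.88 = 183, 161 × 1.10 = 177 and 161 × 1.12 = 180, so 180 is consistent with the stated allowance. The half-width 1.96 × √(0.119 × 0.881 / n) is 5.0 points at n = 161 and 4.7 points at n = 180. The arithmetic is sound. What is in question is the sampling assumption beneath it.

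**2. Frame against target.**

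| | Text | Population |
|---|---|---|
| Abstract, methods | 180 adults | an urban community |
| Abstract, conclusions | anticipated finding | the urban population at large |
| Inclusion criteria | entry condition | residents who bought medicine at a pharmacy outlet during the study |

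The third row is narrower than the first two. Non-buyers and people supplied only elsewhere have zero probability of entry. A larger n shrinks the random error and leaves this gap untouched.

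**3. How large could the distortion be?** The documents give no figure for how much more or less often self-medicators enter the sample, so the ratio r below is an assumption. Let p be the true prevalence, and let a self-medicator be r times as likely to enter as another adult. The expected sample share is then

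share = p·r / (p·r + 1 − p).

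With the plan's p = 0.119:

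| r (assumed) | share | bias (points) | coverage of nominal 95% interval, n = 161 |
|---|---|---|---|
| 0.7 | 0.0833/0.9643 = 8.6% | −3.3 | 69% |
| 1.2 | 0.1428/1.0238 = 13.9% | +2.0 | 88% |
| 1.5 | 0.1785/1.0595 = 16.8% | +4.9 | 61% |
| 2 | 0.2380/1.1190 = 21.3% | +9.4 | 17% |
| 3 | 0.3570/1.2380 = 28.8% | +16.9 | 0.3% |

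Coverage is the normal approximation Φ(1.96 − b/se) − Φ(−1.96 − b/se), with b the bias and se = √(share × (1 − share)/161). At r of about 1.5 the bias alone uses up the ±5 points. Below that it stays inside them, and for r < 1 the sign reverses.

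**4. The SM-history condition.** If the second inclusion sentence applies to survey participants, everyone enrolled has a history of SM or is practising it now. The estimate of ever-SM is then 100% by construction, whatever the frame or sampling method.

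**The case against.** Four points can be made for the plan.

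- **Purposive sampling may concern the interviews only.** The sentence directly follows the one on qualitative interviews, and seeking diverse perspectives is interview language. A condensed article may leave the survey method to the full protocol. This stands as a real possibility. Against it, the sentence goes on to statistical analysis of the data, and no other method is given for the 180. The precision point is therefore conditional. The frame point does not depend on it.
- **The target may be pharmacy customers.** The Introduction ties the influencing factors to Wardha's pharmacy outlets, and the setting is given as communities and pharmacies. That reading is partly available, but the two Abstract statements and the reference population in the Limitations point to the community. The article needs to say which it means.
- **The excluded group may be small.** Data collection runs for 24 months, and one purchase in that time could qualify a person. This limits the likely size of the gap but does not remove it.
- **Sampling bias is already acknowledged.** It is, but only as something that might happen. The entry rule builds it in.

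A reader might go further and infer that the prevalence will be overstated by more than 5 points because frequent buyers are intercepted more often. The documents do not support that. They do not say that people are approached in proportion to their visits, and the use of home medicine inventories suggests contact beyond the counter. The Introduction links chronic disease to greater medicine use, so frequent buyers may largely hold prescriptions, and r could be below 1.

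**Conclusion.** The mismatch between the frame and the claimed population holds on the text: this design can describe medicine purchasers at Wardha pharmacies, not the urban community. That conclusion needs no assumption about size.

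The loss of meaning of the ±5 points, even for purchasers, holds if the purposive sentence applies to the survey, which the article suggests but does not settle. Likewise, the 100% result for ever-SM holds if the SM-history condition applies to the survey.

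The bias is of unknown size and direction. Over assumed ratios of 0.7 to 3, a true 11.9% would appear as 8.6% to 28.8%, an error of −3.3 to +16.9 points. It may plausibly exceed the stated precision, but it cannot be said that it will.

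**What to change.** 1. State the target population as adult medicine purchasers at Wardha pharmacies. Remove the two Abstract statements that attach the prevalence to an urban community and to the urban population at large. Reword the limitation to say that, by design, the sample does not represent the broader adult population.
2. Confine purposive sampling to the in-depth interviews. Recruit the survey from consecutive adult purchasers, or every k-th one, in preset time blocks, and log refusals.
3. Do not apply the criterion of past or current SM to the prevalence survey.
4. Describe the ±5 points as nominal under simple random sampling, and report an interval that allows for clustering by outlet.

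Items 1 and 3 are changes of wording, although 3 means enrolling purchasers without an SM history. Item 2 costs a tally sheet and some discipline in the field. Since the study is described as ongoing, any participants already recruited in another way should be reported as such. Item 4 widens the interval somewhat. The price overall is a narrower conclusion.

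A question on pharmacy visit frequency, used for a weighted sensitivity analysis, is optional.

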## Introduction

Self-medication (SM) is described as the acquisition and ingestion of one or more drugs without consulting a medically qualified physician for diagnosis, treatment, or prescription oversight. It encompasses the use of non-prescription medications by individuals without professional guidance. The wide accessibility of diverse drugs and insufficient and unequal healthcare services contribute to a rise in SM practices in developing nations such as India [1]. Studies carried out in India have observed SM prevalence rates ranging from 29.1% to 55%, varying based on study methodologies and geographical locations [2,3]. Previous studies conducted both domestically and Internationally have identified numerous factors, ranging from geographic isolation to sociodemographic variables, as potential determinants contributing to the widespread practice of SM. However, prior research within this country has not thoroughly examined SM through a socio-psychological lens, which could encompass societal perceptions regarding medication, access to healthcare services, and subsequent care-seeking behaviors among individuals who engage in SM [4].

It is increasingly evident that there is a growing availability of over-the-counter (OTC) medications accessible to the public. The practice of SM with improper usage of drugs could easily result in a variety of complications. The most common and noteworthy among those are adverse drug reactions (ADRs) due to the interactions between various drugs that have been consumed. Many researches have indicated that taking multiple medicines increases the probability of experiencing ADRs. In addition, this risk is further increased in old age as numerous studies have indicated that the consumption of non-prescription drugs could exceed that of prescribed drugs by up to seven times [5]. Hepatic and renal issues, increased fat levels, and exacerbation of pre-existing health conditions could be the most common challenges faced by patients of the elderly age group. Notably, approximately one-third of adult hospital admissions are due to the misuse of non-prescription drugs. Furthermore, the elevated frequency of drug intake increases the risk of experiencing side effects. These side effects encompass various issues, including drug interactions, anaphylactic reactions, impairment of drug tolerance, and the masking of underlying clinical symptoms indicative of serious conditions. Therefore, there is a pressing need for concerted efforts to address this issue and enhance public awareness regarding the potential adverse effects of SM [5].

Nonetheless, SM is not always considered a negative behavior. SM using OTC medications is regarded as a crucial element of self-care. It appears that when the advantages of SM are mentioned, the drugs that a person is permitted to take without having to see a doctor are discussed [6]. The World Health Organization (WHO) states that these products have been produced with strict guidelines and have unique packaging that comes with patient information, all of which can be harmful if ignored [7]. The significance of SM has piqued the interest of healthcare professionals, including physicians and policymakers, particularly as medications transition from prescription-only to OTC availability. The OTC medications and the ways in which they are provided vary by country, and the health systems of each country determine how easy it is to obtain and how often people use them [8].

Self-care has been practical long prior to formal health systems, and it also impacts health outcomes [9]. Since the inception of the primary healthcare movement [10], self-care initiatives in the health sector have increased, fueled by a focus on women's empowerment and the role of self-care in the management of mental health [11] and chronic diseases. Generally, SM is acknowledged to play a vital role in managing minor illnesses. New self-care configurations are becoming feasible because of the rapidly advancing digital technology and expanding global market. While many of these interventions will be subject to regulations, many others will not. This aspect of self-care was underscored by the WHO in 1978 as part of its "Health for All by the Year 2000" initiative, which was adopted in numerous countries worldwide, including Saudi Arabia. Increased prevalence of SM among the general population has been associated with various potential benefits and risks.

Research indicates that the decision to self-medicate is influenced by a multitude of personal, organizational, and environmental factors [12]. Self-care gained attention and notoriety during the COVID-19 pandemic when people started practicing hand hygiene, wearing masks, and performing self-testing at home [13]. SM is a practice observed across all age groups, but a particular focus is directed toward the elderly concerning treatment and medication issues. Numerous studies have highlighted the elderly as the predominant medicine consumers in many countries, a trend also observed in Iran. This heightened medication consumption among the elderly can be attributed to several factors, including the increased prevalence of various diseases associated with aging. Conditions, such as diabetes, cardiovascular disease, and cancer, are prevalent among a significant portion of the elderly population. Additionally, the presence of multiple chronic diseases concurrently, known as comorbidity, is widespread in this age group and often necessitates increased medication usage [7]. SM has long been a prevalent practice within the general populace. This phenomenon is driven by various factors, including the desire for self-care, empathy toward unwell family members, limited access to healthcare services, economic constraints, lack of awareness, misconceptions, widespread advertising, and the availability of medications outside of traditional medical outlets. Additionally, the literature suggests that reasons for engaging in SM include perceptions of illness severity, past experiences with similar illnesses, financial considerations, and difficulties accessing healthcare professionals [14,15]. SM practices should not be universally deemed harmful. OTC medications, available without a prescription, often offer convenience and cost savings for patients. Particularly in remote areas such as hill regions, tribal communities, and other underserved areas with limited access to healthcare professionals, SM remains a crucial recourse for addressing minor symptoms due to the scarcity of medical personnel [16]. Few studies have been conducted at a community level in India to evaluate the prevalence of SM practices. Such studies hold the potential to offer valuable insights into the motivations behind patient’s adoption of this practice. Moreover, they could aid policymakers and regulatory bodies in refining drug regulations, revising the list of essential medicines, and addressing safety concerns related to OTC medications. With this background, the study protocol aims to estimate the prevalence of SM of prescription drugs with their OTC access and the risk practice and identify potential factors that could influence SM practices in pharmacy outlets of Wardha along with reviewing policies pertaining to OTC and prescription drugs and identifying improvements to mitigate the risk practices.

## Materials and methods

Study design, participant, and setting

A convergent parallel mixed method study design with a quantitative component as a cross-sectional study and a qualitative component as an in-depth interview will be used for data collection for a period of 24 months from urban communities and pharmacies of Wardha. Before data collection, informed consent from study participants will be obtained, clearly outlining the purpose of the study, benefits and potential risks, voluntary participation, and the right to withdraw at any time. Ensuring participant confidentiality and privacy while collecting data is essential, and any ethical considerations or limitations in data collection will be carefully addressed to uphold research ethics standards. The study sought approval on 01.03.2024 from the Institutional Ethics Committee of Datta Meghe Institute of Higher Education and Research with reference number DMIHER(DU)/IEC/2024/126 to ensure the research adheres to the ethical guidelines, respects participant rights, and meets established ethical standards and has been registered for the Clinical Trials Registry - India with the registration number CTRI/2024/07/069886.

Inclusion and exclusion criteria

Subjects over 18 years and above who reside in Wardha and visited the pharmacy outlets to purchase medicine(s) during the study will be included in the study. Individuals participating willingly, voluntarily, and providing informed consent, who have a history of SM or are currently engaging in SM practices, and who have the cognitive ability to understand and respond to questions and participate in qualitative interviews. Doctors and healthcare workers who have knowledge of medications, individuals with cognitive impairments, and pregnant or breastfeeding women will be excluded from the study.

Sample size

The sample was calculated based on,

n = [Z2 P (1-P)]/d2

Z is the statistic corresponding to the level of confidence,

P is the expected prevalence,

d is precision (corresponding to effect size).

Sample size calculation

Assumptions:

Precision = 5.0% (0.05)

Prevalence = 11.9% (0.10) [16]

Z = 1.96

N = 1.96*1.96*0.119 (0.881)/0.0025

The final sample size based on the prevalence of 11.9% was 161. Assuming 10.0%-12.0% dropouts, the estimated sample taken was 180.

Data collection tools and methods

Data for this study will be gathered through in-depth semi-structured interviews or questionnaires of 15 to 20 pharmacists and the general population during the study period. These interviews will be administered by the primary researcher, a resident trained in qualitative interview techniques. Additionally, available documents and evidence, like lists of OTC medicines, relevant regulations, prescription records, participants' medication bags, and their home medicine inventories, will be utilized. Each interview will range from 40 to 90 minutes, depending on the respondent's willingness and circumstances. To ensure comprehensive coverage, participants will be given an opportunity to informally converse at the conclusion of the interview, with a prompt such as "Would you like to share anything else?" Subsequent interviews may be scheduled if participants wish to provide further information or if the initial analysis suggests the need for additional data Figure 1. The questionnaire will include Table 1.

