**Figure 1 FIG1:**
[figure not shown]
Schematic flowchart for mixed method study design

**Table 1 TAB1:** Description of the tool included in this study

Section	Details
Part A	Sociodemographic characteristics
	Age
	Place of residence
	Religion
	Marital status
	Level of education
	Occupation
	Family type
	Socioeconomic status (evaluated using Modified B.G. Prasad Scale)
Part B	Self-medication behaviors in the past year
	Patterns of self-medication (e.g., frequency, duration)
	Types of medications used
	Reasons for self-medication (e.g., convenience, cost, perceived need)
Part C	Pharmacist's perspective on self-medication practices
	Inquiry by a doctor to pharmacist
	Pharmacist's observations
	Customer behavior related to self-medication

Data analysis

All collected data will be analyzed using Statistical Package for the Social Sciences (IBM SPSS Statistics for Windows, IBM Corp., Version 23, Armonk, NY). Quantitative data will be presented as mean ± standard deviation, while qualitative data will be expressed as frequencies and percentages. Descriptive statistics will summarize and present sociodemographic characteristics, SM frequencies, patterns, and types of medications used. Measures, such as mean, median, and standard deviation, will be utilized to describe central tendency and variability. Inferential statistics will be employed to analyze relationships and associations between variables. Correlation analysis may explore the degree of association between factors such as age, socioeconomic status, and SM frequency. Furthermore, the chi-square test will assess the impact of demographic variables on SM practices. Group comparisons will be conducted using the student t-test. A p-value <0.05 will be considered statistically significant.

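### The ±5-point precision and the named tests assume independent respondents, although the pharmacy-based entry condition makes grouping by outlet or neighbourhood likely; the precision should be stated as conditional and outlet or site recorded.

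*Protocol article*

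**What the plan says.** Four parts of the protocol article bear on this point.

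- **Entry and setting** (Materials and methods). Eligible adults live in Wardha and "visited the pharmacy outlets to purchase medicine(s) during the study will be included in the study". The design paragraph names both urban communities and pharmacies as sources of data. The Abstract calls the sampling purposive.
- **Aim** (end of the Introduction). One aim is to "identify potential factors that could influence SM practices in pharmacy outlets of Wardha".
- **Sample size**. The single-proportion formula is used without a design-effect term: "N = 1.96*1.96*0.119 (0.881)/0.0025". The article then states: "The final sample size based on the prevalence of 11.9% was 161", followed by "Assuming 10.0%-12.0% dropouts, the estimated sample taken was 180".
- **Data analysis**. Here "the chi-square test will assess the impact of demographic variables on SM practices", groups are compared by Student t-test, and correlation may be used for factors such as age and socioeconomic status. Significance is declared at p<0.05.

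The article gives no number of outlets, no number of respondents per outlet and no ICC. The only related count is the 15 to 20 pharmacists mentioned under data collection.

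**The concern.** Customers of one outlet share its dispensing habits and, often, its neighbourhood. The study concerns prescription drugs obtained over the counter, which depends partly on who dispenses them. If several respondents come from each outlet or area, their answers are likely to be positively correlated, and 161 of them carry less information than 161 independent people.

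Two things are at stake. The precision of the prevalence estimate, which is the sole basis for the sample size, may be worse than stated. Some associations may also be declared at p<0.05 more often than the nominal 5% allows. Both are matters of variance, separate from whether the sample represents Wardha.

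**Working it through.** **1. Inputs from the article.** P = 0.119 (the bracket beside the percentage reads 0.10, but the worked line uses 0.119), d = 0.05, Z = 1.96, 161 completers, 10-12% dropout, 180 recruited.

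**2. Reproducing the plan's figure.** n = Z²P(1−P)/d² = 1.96² × 0.119 × 0.881 / 0.0025 = 161.1, which agrees with 161. For dropout, 161/0.90 = 179 and 161/0.88 = 183, so 180 is reasonable.

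**3. Half-width under independence.** 1.96 × √(0.119 × 0.881 / n) gives ±5.00 points at n = 161 and ±4.73 at n = 180.

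**4. Is there a reserve for clustering?** After 10-12% dropout, 180 leaves 162 to 158 completers, so the increase is used up by dropout. If all 180 complete, the design effect (DE) that can be absorbed is 180/161.1 = 1.12.

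**5. Half-width with grouping.** DE = 1 + (m − 1) × ICC, where m is the number of completers per outlet; the half-width is 5.00 × √DE. Assumptions: 15 to 20 outlets (the pharmacist count as proxy), equal numbers per outlet, and ICC from 0 to 0.10. With 161 completers, m = 161/20 = 8.05 or 161/15 = 10.73.

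| ICC | Outlets | DE | Effective n | Half-width (points) |
|---|---|---|---|---|
| 0 | any | 1.00 | 161 | ±5.0 |
| 0.01 | 20 | 1.07 | 150 | ±5.2 |
| 0.01 | 15 | 1.10 | 147 | ±5.2 |
| 0.05 | 20 | 1.35 | 119 | ±5.8 |
| 0.05 | 15 | 1.49 | 108 | ±6.1 |
| 0.10 | 20 | 1.71 | 94 | ±6.5 |
| 0.10 | 15 | 1.97 | 82 | ±7.0 |

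**6. The same with all 180 completing.** Now m = 9 or 12. At ICC 0.01, DE = 1.08 to 1.11 and the half-width is 4.73 × √DE = ±4.9 to ±5.0, so the target is met. At ICC 0.05, DE = 1.40 to 1.55 and the half-width is ±5.6 to ±5.9, so it is not.

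**7. Tests.** For a factor that is constant within each outlet, the true error rate of a nominal 5% test is about 2[1 − Φ(1.96/√DE)]. This gives about 6% at ICC 0.01, 9-11% at 0.05 and 13-16% at 0.10. For a factor that is only partly clustered, the inflation depends on the product of the two ICCs. With 15 outlets, an outcome ICC of 0.05 and a factor ICC of 0.3, DE = 1 + 9.73 × 0.05 × 0.3 = 1.15 and the error rate is about 6.7%. For a factor that varies within outlets there may be no inflation, and an unadjusted test can even be conservative.

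**The case against.** The strongest reply is that clustered recruitment is inferred. A pharmacy purchase is an eligibility condition, not a sampling stage, and communities are named as a source too. Interviews of 40 to 90 minutes and the use of home medicine inventories fit contact in the community at least as well as enrolment at a counter. This stands: a reader might infer that outlets are the sampling units, but the article does not say so. Recruitment by neighbourhood would group respondents in the same way, however, and the formula allows for neither.

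The size is also wholly assumed. One can reach ±7.9 points, with a nominal 95% interval covering about 78%, but only with 10 outlets and ICC 0.10. Ten is below the sole proxy in the text, so those extremes should not be presented as the expected loss.

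A reader might further infer that the planned p-values are too small in general. The article does not support that. The named tests concern person-level factors and no test of an outlet-level factor is described. Part C of the questionnaire records pharmacists' views and is no evidence of correlation among customers. Inflation is plausible for place of residence or socioeconomic status, less so for factors that vary within outlets.

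Finally, the article is condensed, and a cluster adjustment may stand in an analysis plan not shown. That could answer the point about the tests. It does not answer the sample size, which is printed in full and rests on independence.

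**Conclusion.** The point holds in conditional form. The ±5-point precision is correct arithmetic under independence and may be optimistic under the recruitment that the article suggests. With 15 to 20 outlets and 161 completers, the loss runs from about 0.2 points (ICC 0.01) to about 2 points (ICC 0.10). It is nil if ICC is 0, and absorbed if all 180 complete and the design effect is at most about 1.12. Against an expected prevalence of 11.9%, ±6 to ±7 points is more than half the estimate, so the upper part of the range matters. False-positive inflation is possible only for factors that cluster by outlet or area. The number of outlets and the ICC are assumptions throughout.

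This is a worthwhile correction, not a fatal flaw, and not the only threat to the prevalence estimate. Purposive sampling, and the requirement of past or current self-medication, introduce bias that no design effect repairs.

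**What to change.** - Record the outlet or recruitment site on every questionnaire. The study is described as ongoing, and this information may not be recoverable later.
- Report the prevalence with a 95% confidence interval that is robust to clustering by outlet or site.
- Replace the plain tests by cluster-adjusted ones: Rao-Scott chi-square, or GEE or cluster-robust regression, with a small-sample correction because the clusters are likely to be few.
- State how and where respondents are enrolled, say that ±5 points assumes independence, and give the half-width for an assumed design effect. At 1.5, for example, it is 5.00 × √1.5 = ±6.1 points.

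The cost is one extra field, slightly more analysis and somewhat wider reported intervals. No extra subjects are needed. If respondents turn out not to be grouped, the identifier lets the sponsor show it, and little is lost.
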